### 2.3. Variables

All assessments will be carried out within 7 days and will be monitored and quality controlled by a researcher independent of the sponsor.

#### 2.3.1. Sociodemographic variables

Data on age, sex, marital status, educational level, and occupation will be collected when participants are accepted into the study. A history of hypertension, dyslipidemia, diabetes, hypothyroidism, other diseases, and drug use will be documented.

#### 2.3.2. Anthropometric measurements

Body weight will be measured twice using an approved electronic scale (Seca 770 medical scale and measurement systems, Birmingham, United Kingdom), with the patient dressed in light clothing and barefoot. BMI will be calculated as the weight (kg) divided by the height squared (m^2^). The waist circumference will be measured with a flexible, graduated tape measure with the patient standing up and undressed. Body composition will be determined using the InBody 230 monitor (InBody Co. Ltd., Seoul, Korea), which provides body composition analysis information. Clinical blood pressure (BP) will be measured three times, with the average of the last two times being recorded, using a validated Omron M10-IT model sphygmomanometer (Omron Healthcare, Kyoto, Japan). Measurements will be made on the dominant arm of the participant in a sitting position after at least 5 min of rest with an appropriately sized cuff, which was determined by measuring the circumference of the upper arm and following the recommendations of the European Society of Hypertension (ESH) (31).

#### 2.3.3. Habits and lifestyles

##### 2.3.3.1. Diet

Participants' eating habits will be assessed using a 137-item semi-quantitative food frequency questionnaire (FFQ) previously validated in Spain (32). The FFQ is based on typical portion sizes that will be multiplied by the frequency of consumption of each food. The FFQ estimates food consumption frequency for the year before the interview and is divided into *nine* consumption frequency categories ranging from never to more than *six* servings per day. This will be used to estimate the daily intake of macronutrients and micronutrients.

The Mediterranean Diet Adherence Screener (MEDAS) (33), developed by the PREDIMED study group, will be used to assess adherence to the Mediterranean diet. Each question will be scored as 0 or 1. Adequate adherence to the Mediterranean diet will be assumed when the total score is ≥9 points. Food consumption will be recorded during a normal week with the application developed in the EVIDENT study (34) (registry number 00/2014/2207).

##### 2.3.3.2. Physical activity and sedentary behavior

Physical activity will be measured using both objective and subjective methods. *The ActiGraph-GT3X accelerometer* (ActiGraph, Shalimar, FL), which has been previously validated (35), will be used to measure the physical activity of the subjects for seven consecutive days, including step counts and levels of moderate-to-vigorous physical activity. The original data from the accelerometers will be collected at a frequency of 30 Hz. Before the test, the accelerometer will be initialized, and the correct way of wearing the accelerometer and matters needing attention will be discussed.

The specific requirements for wearing it are as follows: (a) the accelerometers are fixed at the waist and positioned on another axillary line at the iliac crest level of the right or left hip; (b) wearing the accelerometer continuously for 7 consecutive days except during bathing or swimming. The accelerometers will record activity during the day and at night. If the number of days is <3 days a week or the time of wearing is <8 h a day, the data will be considered invalid. Data will be recorded at 1-min intervals. The intensity of the physical activity (low, moderate, or high) will be determined according to the cut-off points proposed by Freedson et al. (36).

The *International Physical Activity Questionnaire-Short Form (IPAQ-SF*) (37) will also be used to assess physical activity. The short form (nine items) categorizes physical activity for the last 7 days at three levels of intensity: (1) intense physical activity, (2) moderate-intensity activity, and (3) light activity. The IPAQ is a self-reported questionnaire that evaluates sitting and active time in the last 7 days, differentiating between walking, moderate-intensity, and vigorous-intensity activities according to the energy expenditure estimated for each of them [3.3, 4.0, and 8.0 metabolic equivalents of task (MET), respectively].

Participants reported their sedentary behaviors in total daily sitting time using the *Marshall Sitting Questionnaire (MSQ)* (38). This validated questionnaire assesses sitting time in hours and minutes on weekdays and weekend days across five domains: transportation, work, television watching, at-home computer use, and leisure not specified in other domains. In daily sitting hours, SB was calculated by summing the sitting time for each domain.

##### 2.3.3.3. Tobacco and alcohol consumption

A standardized questionnaire will be used to assess tobacco and alcohol consumption. Smoking status will be assessed through a questionnaire of *four* standard questions adapted from the WHO MONICA study (39). Study participants will be classified as current smokers or non-smokers (never or >1 year without smoking). To assess drinking, a structured questionnaire will be used to record the number of alcoholic beverages drunk in the previous week, the grams/week consumed will be estimated, and the patient will be classified as teetotal, low risk, intermediate risk, or high risk according to the criteria of the Spanish Ministry of Health (40).

#### 2.3.4. Vascular structure and function

##### 2.3.4.1. Carotid-femoral pulse wave velocity and central augmentation index

These parameters will be estimated using the SphygmoCor System (AtCor Medical Pty Ltd., Head Office, West Ryde, Australia). Carotid and femoral artery pulse waves will be analyzed with the patient in a supine position using the SphygmoCor System, estimating the delay compared with the ECG wave and calculating carotid-femoral pulse wave velocity (cf-PWV) in m/s. Distance will be measured with a measuring tape from the sternal notch to the carotid and femoral arteries at the sensor location. With the patient sitting and resting his/her arm on a rigid surface, pulse wave analysis will be performed with a sensor in the radial artery, using a mathematical transformation to estimate the aortic pulse wave and Central Augmentation Index (CAIx) (41).

##### 2.3.4.2. Cardio-ankle vascular index, brachial-ankle PWV, and ankle-brachial index

These parameters will be estimated using the VaSera device VS-2000 (Fukuda Denshi Co, Ltd., Tokyo, Japan). Cardio-ankle vascular index (CAVI) values will be automatically calculated by substituting the stiffness parameters in the following equation to detect the vascular elasticity and the cardio ankle PWV: stiffness parameter β = 2ρ × 1/(Ps–Pd) × ln (Ps/Pd) × PWV 2, where ρ is the blood density, Ps and Pd are SBP and DBP in mmHg, and PWV is measured between the aortic valve and ankle. The brachial-ankle PWV (ba-PWV) will be estimated using the following equation: ba-PWV = {[0.5934 × height (cm) + 14.4724]}/tba, where tba is the time the same waves were transmitted to the ankle (42). For this study, the mean ankle-brachial index (ABI), CAVI, and ba-PWV obtained will be considered. CAVI will be classified as normal (CAVI < 8), borderline (8 ≤ CAVI < 9), and abnormal (CAVI ≥ 9) (43).

##### 2.3.4.3. Central and peripheral augmentation index by the wrist-worn device

The wrist-worn device was developed by Microsoft Research (Redmond, Washington, USA) and validated by our team (44). We will use this device to make a short recording of the radial pulse wave, from which peripheral augmentation index (PAIx) and CAIx will be obtained. PAIx will be calculated as [second peak SBP (SBP2)–]/(first peak SBP-DBP) x 100 to yield a percentage (%) value, and CAIx will be calculated using the following formula: central augmentation pressure x 100/pulse pressure. Participants will be examined in a seated position, with the arm resting on a firm surface at heart level, after 10 min of rest.

##### 2.3.4.4. Assessment of vascular structure by carotid intima-media thickness

Measurements of carotid intima-media thickness (C- IMT) will be made by investigators trained in the common carotid after the examination of a 10 mm longitudinal section at 1 cm from the bifurcation. They will perform measurements in the proximal and distal walls of the lateral, anterior, and posterior projections, following an axis perpendicular to the artery to discriminate two lines, one for the intima blood interface and the other for the media-adventitious interface. The measurements will be obtained with the participant lying down, with the head extended and slightly turned opposite to the examined carotid artery. Following the ESC/ESH Guidelines for the Management of Arterial Hypertension (31), the measurement is considered pathological if the C-IMI <0.9 mm, the atheromatous plaque diameter is >1.5 mm, or the focal increase is 0.5 mm or 50% of the adjacent IMT (31).

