**Methods and analysis:**

MIVAS III is a multicenter cross-sectional study that will take place in the Iberian Peninsula. One thousand subjects aged between 45 and 74 years without cardiovascular disease will be selected. The main variables are demographic information, anthropometric measurements, and habits (tobacco and alcohol). Dietary patterns will be assessed using a frequency consumption questionnaire (FFQ) and the Mediterranean diet adherence questionnaire. Physical activity levels will be evaluated using the International Physical Activity Questionnaire (IPAQ), Marshall Questionnaire, and an Accelerometer (Actigraph). Body composition will be measured using the Inbody 230 impedance meter. Arterial aging will be assessed through various means, including measuring medium intimate carotid thickness using the Sonosite Micromax, conducting analysis with pulse wave velocity (PWA), and measuring pulse wave velocity (cf-PWV) using the Sphygmocor System. Additional cardiovascular indicators such as Cardio Ankle Vascular Index (CAVI), ba-PWV, and ankle-brachial index (Vasera VS-2000^®^) will also be examined. The study will analyze the intestinal microbiota using the OMNIgene GUT kit (OMR−200) and profile the microbiome through massive sequencing of the 16S rRNA gene. Linear discriminant analysis (LDA), effect size (LEfSe), and compositional analysis, such as ANCOM-BC, will be used to identify differentially abundant taxa between groups. After rarefying the samples, further analyses will be conducted using MicrobiomeAnalyst and R v.4.2.1 software. These analyses will include various aspects, such as assessing α and β diversity, conducting abundance profiling, and performing clustering analysis.

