Although intestinal architecture, genetically defined traits, and age are the factors most strongly influencing the composition of the intestinal microbiome (8), diet and lifestyle are likely the major causes of interindividual variation in its composition in humans. A multitude of factors, such as restrictive diets and strict vegan or gluten-free diets, have been shown to change the intestinal microbiota and can contribute to intestinal dysbiosis (3). Obesity is related to reduced fecal microbial diversity, just as a high-salt diet leads to dysbiosis (3). Physical exercise also has a positive impact on the biodiversity of the microbiota, as some studies on animals and humans have shown (4, 9). Nevertheless, while evidence suggests that the microbiota plays a key role in maintaining systemic nitric oxide (NO) homeostasis, causal inferences regarding healthy aging are limited (10). There are also no conclusive studies analyzing the relationship between oral microbiomes and different lifestyles.

The gut microbiome changes across the lifespan, reaching maturity at 2–3 years, remaining relatively stable during adulthood, and beginning to change as the host starts to age (11). During the aging process, the gut microbiome becomes unstable and experiences a decrease in diversity (12). The loss of bacterial diversity in the intestine of older adults has been associated with increased frailty and reduced cognitive performance, as well as the institutionalization of aging individuals and reduced physical activity (13). Dysbiosis has been associated with several diseases and conditions prevalent in older adults, including type 2 diabetes, frailty, insulin resistance, atherosclerosis, hypertension, Alzheimer's disease, and others (4). Some associations have also been found with parameters of arterial aging, such as an increase in intima-media thickness (IMT) with the abundance of *Serratia* and *Blautia* and a greater presence of *Bacteriodes* associated with a higher pulse wave velocity in subjects without diabetes (14). In a cohort of women in the UK, an inverse association between the diversity of the intestinal microbiota and arterial stiffness was found (15). Although there are no specific studies on the oral microbiome and vascular aging, evidence would suggest that oral bacteria play an important role in mediating the beneficial effects of nitrate-rich foods on blood pressure (16) and, thus, vascular function.

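### The carotid IMT cut-off is printed in the wrong direction (below 0.9 mm counts as pathological), which contradicts the other criteria in the same sentence

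*Protocol article*

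**What the plan says.** The Abstract names carotid intima-media thickness first among the measures of arterial aging: "Arterial aging will be assessed through various means, including measuring medium intimate carotid thickness".

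Section 2.3.4.4 describes how it is measured and then gives a rule for calling the result pathological, attributed to the cited hypertension guideline (reference 31). The rule has three parts joined by 'or'. The first two are: "the measurement is considered pathological if the C-IMI <0.9 mm, the atheromatous plaque diameter is >1.5 mm". The third is: "or the focal increase is 0.5 mm or 50% of the adjacent IMT".

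The Introduction gives the direction in which the authors read this measure. It refers to "parameters of arterial aging, such as an increase in intima-media thickness (IMT" and reports its association with certain bacterial genera.

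No other section restates the IMT threshold or corrects it.

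**The concern.** A three-part 'or' rule makes sense only if each part points towards the same condition. Here two parts flag thickening and one flags thinness. Read literally, the rule calls a thin wall diseased, calls a locally thickened wall diseased, and calls a wall that is thick throughout normal.

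This is an operational definition of an outcome, not background text, and it is the only statement of the rule in the article. If it reaches a derived variable unchanged, participants with thin walls are pooled with plaque carriers in the pathological group. The normal group is then made up only of people at or above 0.9 mm who have no plaque or focal lesion. An association of lifestyle or microbiota with that variable could not be read as an association with arterial aging. Section 2.4 also says that those who run the analyses are blinded to clinical data, which could make a wrong label harder to notice.

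**Working it through.** No sample size, power or error-rate figure depends on this rule, so there is no plan figure to reproduce. The check is one of logic.

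**Step 1. Direction of each statement.**

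| Place | Criterion or statement | Direction that counts as worse |
|---|---|---|
| 2.3.4.4, first criterion | C-IMT below 0.9 mm | thinner |
| 2.3.4.4, second criterion | plaque above 1.5 mm | thicker |
| 2.3.4.4, third criterion | local increase of 0.5 mm, or of 50% relative to the adjacent wall | thicker |
| Introduction | a rise in IMT as a parameter of arterial aging | thicker |

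The first row is the only one that disagrees. As a side check on how the article writes cut-offs, section 2.3.4.2 calls CAVI of 9 or more abnormal, so the neighbouring vascular cut-off also runs upward.

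**Step 2. Is this an artefact of text extraction?** Probably not. The 'greater than' sign survives in the plaque criterion of the same sentence, and section 2.3.4.2 keeps its inequality signs.

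**Step 3. Apply the rule to example carotids.**

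| Carotid | As printed (<0.9 mm) | Sign reversed (>0.9 mm) |
|---|---|---|
| 0.7 mm, no plaque, no focal increase | pathological | normal |
| 1.1 mm throughout, no plaque, no focal increase | normal | pathological |
| 1.1 mm with a 2.0 mm plaque | pathological | pathological |

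**Step 4. Who is affected in general.** Let L mean that plaque above 1.5 mm or a qualifying focal increase is present.

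- Printed rule: pathological = (IMT < 0.9) or L.
- Reversed rule: pathological = (IMT > 0.9) or L.
- With L, both rules give pathological, so nothing changes.
- Without L, the two rules give opposite labels, except at exactly 0.9 mm, where both give normal.

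If p is the share of participants with L, the number whose label differs is 1,000 × (1 − p), less anyone at exactly 0.9 mm. The documents give neither p nor the distribution of IMT, so this cannot be reduced to a single figure. It does not depend on how many participants fall below 0.9 mm.

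**The case against.** The strongest reply is that this is a slip of the pen. The abbreviation in the same sentence is also mistyped, the rule contradicts itself on its face, and it claims to follow a published guideline. A programmer would probably notice, and nothing shows that any data have been coded this way. That is fair, and it is why the consequences are stated as conditional on literal coding. It does not remove the error from the definition.

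A second reply is that no analysis in section 2.4 names a binary IMT outcome. The mediation analysis of arterial aging uses linear regression, which suits continuous measures. Logistic models are mentioned, but not for IMT. This stands: binary use is possible, not stated.

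Several stronger readings are tempting, but the documents do not support them:

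- *All thickened carotids would be classed as normal.* They would not. Those with plaque above 1.5 mm or a qualifying focal increase remain pathological through the other two criteria.
- *Every odds ratio would become its reciprocal, for example 1.5 becoming 1/1.5 = 0.67.* That holds only if the two labels are swapped for everyone. Under the three-part rule the participants with a lesion keep their label, so the result is a mixture and not a mirror image.
- *The sample size is affected.* The vascular-aging groups of 471 and 471 in section 2.2 are not defined by IMT.
- *Arterial aging as a whole is compromised.* C-IMT is one of several measures. The definitions of cf-PWV, CAVI, ba-PWV and ankle-brachial index are untouched.

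**Conclusion.** Wrong as written. The inequality for C-IMT contradicts the two other criteria in its own sentence and the Introduction, and this can be shown from the article alone.

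The damage is confined to the pathological/normal classification of the carotid measurement. It arises only if that variable is derived as printed and then used. In that case participants without plaque or focal increase are labelled the wrong way round, and the combined variable has no clear meaning. Continuous C-IMT analyses do not change.

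The conclusion assumes that the three criteria are alternatives, as the 'or' indicates, and that the sign was printed as extracted. The direction does not rest on the cited guideline, which is not at hand. The exact cut-off and the handling of a value of exactly 0.9 mm do, and remain to be confirmed there.

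**What to change.** In section 2.3.4.4, reverse the inequality so that the first criterion reads C-IMT >0.9 mm and all three criteria point towards thickening. Confirm the cut-off, including whether 0.9 mm itself is included, against reference 31. Correct C-IMI to C-IMT in the same sentence. Before analysis, check any code that derives a pathological/normal carotid variable. The three example carotids above can serve as test cases.

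The cost is one character, one abbreviation and a short code check. No data collection, sample size or analysis method changes.

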#### 2.3.5. Target organ damage

##### 2.3.5.1. Renal assessment

Renal damage will be assessed by the estimated glomerular filtration rate using the Chronic Kidney Disease Epidemiology Collaboration (CKD-EPI) (45) and albumin–creatinine ratio, following the criteria of the ESC/ESH Guidelines for the Management of Arterial Hypertension (31).

##### 2.3.5.2. Cardiac assessment

Cardiac damage will be assessed using an ECG device. Left ventricular hypertrophy will be defined as a Sokolow-Lyon index > 3.5 mV or Cornell VDP > 2,440 mV × ms (31).

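### The Cornell threshold for left ventricular hypertrophy pairs a number and a unit that do not fit together, and used literally it would identify almost no one

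*Protocol article*

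**What the plan says.** Section 2.3.5.2 (Cardiac assessment) is the only cardiac entry under target organ damage. It opens with "Cardiac damage will be assessed using an ECG device" and then fixes a two-part rule, citing reference 31: "Left ventricular hypertrophy will be defined as a Sokolow-Lyon index > 3.5 mV or Cornell VDP > 2,440 mV × ms". Meeting either part is enough.

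The Cornell criterion appears nowhere else in the article. No other section restates it in a different unit, corrects it, or gives a QRS duration, an ECG calibration, a device model or an output unit for the ECG.

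**The concern.** The two criteria stand side by side and both use millivolts. One is a voltage and the other is a voltage multiplied by a duration in milliseconds. Dividing the second by any ordinary QRS duration should therefore give a voltage of roughly the same order as the first. It does not: the Cornell figure comes out several times larger.

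This is a decision threshold in an outcome definition, so the mismatch can reach the data. If "Cornell VDP > 2,440 mV × ms" is programmed as printed, one arm of an either/or rule stops working in practice. Anyone who qualifies only through that arm is counted as not having hypertrophy. The binary variable is then undercounted, and its associations with the microbiota rest on the Sokolow-Lyon arm. The study is multicenter and the section gives no output unit, so centers or analysts could also resolve the printed unit in different ways.

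**Working it through.** **Inputs from section 2.3.5.2**
- Cornell product threshold: 2,440, in mV × ms.
- Sokolow-Lyon threshold: 3.5 mV.
- Combination rule: either one suffices.

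**Assumptions (not in the article)**
- QRS duration: 80 to 120 ms as the main range, 60 to 200 ms as a wide range.
- ECG calibration: 10 mm per mV, used only in step 3.

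The article gives the Cornell threshold as a constant without a derivation, so there is no calculation of its own to reproduce. The check is one of units.

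**Step 1. Voltage needed if the unit is read literally**

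Required voltage = 2,440 / QRS duration. Ratio = required voltage / 3.5 mV.

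| Assumed QRS (ms) | Required voltage (mV) | Ratio to 3.5 mV |
|---|---|---|
| 60 | 2,440/60 = 40.7 | 11.6 |
| 80 | 2,440/80 = 30.5 | 8.7 |
| 100 | 2,440/100 = 24.4 | 7.0 |
| 120 | 2,440/120 = 20.3 | 5.8 |
| 150 | 2,440/150 = 16.3 | 4.6 |
| 200 | 2,440/200 = 12.2 | 3.5 |

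**Step 2. The same question in reverse**

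QRS duration needed = 2,440 / voltage.
- At 3.5 mV: 2,440/3.5 = 697 ms.
- At 5 mV: 2,440/5 = 488 ms.

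Both lie far outside even the wide range in step 1, so the mismatch does not depend on the QRS value chosen.

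**Step 3. Does another unit remove the mismatch?**

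If the same number were in mm × ms, then at 10 mm per mV:

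2,440 mm × ms × 0.1 mV/mm = 244 mV × ms.

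- 80 ms: 244/80 = 3.05 mV
- 100 ms: 244/100 = 2.44 mV
- 120 ms: 244/120 = 2.03 mV

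These are of the same order as the neighbouring 3.5 mV. A unit slip would therefore explain the figure. So would a tenfold slip in the number with the unit left as printed, because 244 mV × ms and 2,440 mm × ms are the same threshold under this calibration. The arithmetic cannot tell the two apart.

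**The case against.** The strongest reply concerns weight and certainty, since the division itself is not in doubt.

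- **Weight.** Hypertrophy is peripheral. The abstract's list of main variables and measurements does not include the ECG. The sample size in section 2.2 rests on the Shannon index and on vascular aging, and the mediation analysis in section 2.4 concerns arterial aging. The Discussion and Summary do name cardiovascular target organs, so the variable is not irrelevant, but it is one component beside renal, retinal and cognitive measures. This stands and limits the severity.
- **Certainty of the effect.** A reader might infer that the Cornell criterion can never be met, that hypertrophy will rest on Sokolow-Lyon alone, and that the Cornell-positive count among 1,000 participants will be zero. The article does not support that. The loss of the Cornell arm depends on the printed unit being applied literally, and a device or analyst working in another unit could classify correctly despite the text. No distribution of Cornell voltage is given, so no count can be computed. Also, "Sokolow-Lyon index > 3.5 mV" is a cut-off for a different index and not a ceiling on Cornell voltage. The ratios show an implausible scale; they do not prove impossibility.
- **The correction.** A reader might also infer that the unit should simply become mm × ms. That fits the arithmetic, but it depends on an assumed calibration. The article shows only that number and unit disagree, and the cited guideline is not available here.

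What the reply does not remove is the mismatch itself. It survives every QRS duration from 60 to 200 ms, and nothing elsewhere in the article corrects it.

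**Conclusion.** The point holds as an error in an outcome definition: the Cornell number and unit in section 2.3.5.2 cannot both be right on any QRS duration tried. The threshold is out of scale with its neighbour by a factor of 5.8 to 8.7 at an assumed 80 to 120 ms, and by 3.5 at an assumed 200 ms.

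The effect on the data is conditional. Coded as printed, the rule would lose nearly all Cornell-positive participants; read in another unit, it may work as intended. How many participants are affected cannot be derived from the article.

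Severity is moderate to minor. The main objectives and the sample size do not depend on this variable.

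**What to change.** Reconcile the number and the unit in section 2.3.5.2 with the guideline cited there (reference 31), and print the pair that the guideline supports. State the unit in which the ECG device reports or exports the Cornell product. Check that the export from every center and the derivation code use that unit before hypertrophy is derived. If any participants have already been classified, rerun the derivation from the stored ECG values.

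The cost is one line of text and a short code check. No change to data collection, sample size or the analysis models follows from it.
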